## Abstract

Despite substantial progress, Bangladesh still has a high rate of maternal deaths owing to difficulties during pregnancy, delivery, and the postpartum period. Increasing facility delivery is mandatory to reach the goal of bringing down the MMR to <70 deaths/100,000 live births by 2030. In the era of digitalization, the introduction of e-registration and mHealth may aid the government in reaching this target. The southern part of Bangladesh is a hazard-prone area, where service uptake from institutions is low. This study aims to determine the effect of an e-registration tracking system and mHealth counseling on institutional deliveries to pregnant mothers in hazard-prone areas of southern Bangladesh. We will conduct an open-label, two-arm, non-randomized controlled cluster trial for six months and use three hazard-prone areas for intervention and another three hazard-prone areas for control. We will collect data at baseline and end-line of the study period using a structured questionnaire. We will enroll at least 268 pregnant mothers from the intervention and 268 pregnant mothers from the control areas after screening based on the inclusion and exclusion criteria. Pregnancy information will be obtained from the Family Welfare Assistant register. The respondents of the intervention arm will be registered in the e-Registration system, and receive voice call and text messages from the midwives to have their deliveries done in healthcare facilities. We will follow the participants until their delivery and exclude those respondents from the study who will have post-dated delivery, migrate out, lost to follow-up, or die during the study period. Random-intercept mixed-effect logistic regression will be performed to explain the relationship of e-registration and mHealth package with institutional delivery. Institutional delivery is still uncommon in Southern Bangladesh despite several interventions. Innovative approaches like e-registration and mHealth counseling may be helpful to bring women to health facilities. The findings from the study might enable the policy makers of Bangladesh to integrate the intervention package into the existing healthcare system. This experiment is registered in the open science framework.

**Clinical trial registration:** Registration number: DOI 10.17605/OSF.IO/YZE5C) and https://www.clinicaltrials.gov/ (registration number: NCT05398978.

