### Study design and setting

The study will be an open-label two-arm non-randomized controlled cluster trial for six months where Chandpur Sadar, Kachua, and Faridganj sub-districts will be the intervention arm as MIS unit; DGFP will initiate the eMIS registration system in these three sub-districts of Chandpur district. Chandpur is a district under the Chattogram division, located in the Southern part of Bangladesh, and is a disaster-prone area. There are 14 unions in Chandpur Sadar, 12 in Kachua, and 15 in the Faridganj sub-districts of Chandpur [18]. The Government of Bangladesh has taken the initiative to implement various models in different districts, such as the Maternal, Newborn, and Child Survival (MNCS) and Maternal, Newborn and Child Health (MNCH) project by UNICEF; Maternal, Newborn Health Initiative (MNHI) through joint UN initiatives; and USAID supported program MaMoni. But none has chosen Chandpur district as their project implementation site. Again, the majority of the social and health indicators of Chandpur Sadar, Faridganj, and Kachua sub-districts are below national estimates mostly due to the hazard-prone nature of these areas [18]. So, we have chosen these three sub-districts of Chandpur district as intervention areas. The e-registration and mHealth services are not available in Bhola District. In addition, Bhola is likely to be similar to Chandpur, especially in terms of its geographical location, susceptibility to disasters, and health care and care-seeking practices of the inhabitants [18]. So, we have selected the Bhola Sadar, Charfesson, and Lalmohan sub-districts of the Bhola district as the control arm. Bhola Sadar has 13 unions, Charfesson has 14 unions, and Lalmohan has 9 unions [19]. Unions will be considered as cluster units, and individual study participants will be the sample unit.

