### Sample size

We have planned to recruit and then follow up a minimum of 268 pregnant mothers in the intervention areas and 268 pregnant mothers in the control areas. According to a study conducted in Ethiopia, the implementation of mHealth services using both voice calls and text messages increased facility delivery by 14.7% in the intervention group compared to the control group (43.1% compared to 28.4%; AOR: 1.98 (95%CI: 1.53, 2.55)) [4]. We decided on this proportion we need to determine the number of respondents for our study at a 5% level of error margin and 80% power. Using the formula below we determined the sample size to be 268 for each of the intervention and control groups.

$$n=\frac{p_{1}(100-p_{1})+p_{2}(100-p_{2})}{{\left(p_{1}-p_{2}\right)}^{2}}x{\left(z_{\alpha }+z_{\beta }\right)}^{2}x\;g$$

-----------------------------------------

Here,

p_1_ = 53.8% (Proportion of institutional delivery in Bangladesh) [19]

p_2_ = 68.5% (Proportion of institutional delivery following intervention assuming a 14.7% increase) [4]

z_α_ = 1.96 (at 5% error margin)

z_β_ = 0.85 (at 80% power)

g = 1.50 (design effect)

non-response rate = 5%

-----------------------------------------

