### Data management and analysis plan

We will analyze the data in R 4.1.2. We will do a frequency distribution and proportion analysis for categorical variables, and for continuous variables, we will perform a mean and standard deviation analysis. We will use chi-square test to make comparison between the groups. Finally, a random-intercept mixed-effect logistic regression model will be fitted to explain the relationship of e-Registration and mHealth package with institutional delivery, where the union will be included as the random intercept. An adjusted odds ratio with p-value less than 0.05 will be considered statistically significant. 95% confidence interval will be calculated from the logistic regression model.

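### The package is assigned by whole sub-district, three per arm and one district per arm, but the primary test counts the union as the only cluster level, so its p-value and confidence interval are too favourable unless outcome does not vary between these areas

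*Protocol article*

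**What the plan says.** Under Study design and setting, the article allocates areas without randomization. It states "where Chandpur Sadar, Kachua, and Faridganj sub-districts will be the intervention arm as MIS unit" and, for control, "we have selected the Bhola Sadar, Charfesson, and Lalmohan sub-districts of the Bhola district as the control arm". The Abstract agrees: the trial will "use three hazard-prone areas for intervention and another three hazard-prone areas for control". The Introduction places the counselling midwives at three facilities, one for each intervention sub-district.

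The same design section then names a lower level as the cluster: "Unions will be considered as cluster units, and individual study participants will be the sample unit". The counts are "There are 14 unions in Chandpur Sadar, 12 in Kachua, and 15 in the Faridganj sub-districts of Chandpur" and "Bhola Sadar has 13 unions, Charfesson has 14 unions, and Lalmohan has 9 unions".

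The Data management and analysis plan follows the union. The primary model is a random-intercept logistic regression "where the union will be included as the random intercept". Significance is judged on the adjusted odds ratio at p < 0.05, and the 95% confidence interval comes from the same model. The Sample size section gives "g = 1.50 (design effect") with no intracluster correlation (ICC), cluster size or level. The article has no sub-district or district term, and its Discussion names recall bias as the only limitation.

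**The concern.** A random intercept protects the arm comparison only against variation at the level it represents. Here no union was assigned separately from its neighbours: all unions of a sub-district share the arm, and all three sub-districts of an arm share the district. The union-only model nevertheless treats the unions as the independent units behind the arm effect.

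If sub-districts differ in facility delivery for reasons other than the package (type of hospital, distance, roads, local custom), those differences do not average out over unions. They remain in the arm difference while the standard error ignores them. An ordinary difference between areas could then be reported as a significant effect of the package, in a trial whose Discussion hopes to inform government roll-out. The stated 80% power rests on the same view of the clusters.

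**Working it through.** **Inputs from the article.** Proportions 53.8% and 68.5%; z-values 1.96 and 0.85; design effect 1.5; non-response 5%; 268 women per arm (Sample size). Unions: 14 + 12 + 15 = 41 intervention and 13 + 14 + 9 = 36 control, 77 in all (Study design and setting).

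**Assumed, because the article gives none.** Between-sub-district or between-district SDs of 3, 5 and 8 percentage points, with no covariate adjustment.

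**1. The stated sample size.**
- 0.538 × 0.462 + 0.685 × 0.315 = 0.4643.
- 0.4643 / 0.147² × (1.96 + 0.85)² = 169.67.
- 169.67 × 1.5 = 254.5; divided by 0.95 this is 267.9, so 268.

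The figure reproduces. The question is the level of clustering, not the arithmetic.

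**2. What a design effect of 1.5 covers.** With 254.5 analysed women per arm there are about 6.2 (41 unions) or 7.1 (36 unions) per union. The implied union ICC, 0.5/(m − 1), is about 0.10 or 0.08. Read at sub-district level, with about 85 women each, 1.5 covers an ICC of only 0.5/84 ≈ 0.006.

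**3. Type I error of the union-level test.** The null standard error is √(1.5 × 2 × 0.538 × 0.462 / 254.5) = 5.41 points (variance 29.3). Three sub-districts per arm add 2·SD²/3 to the true variance; one district per arm adds 2·SD². The test still uses 5.41, so the type I error is 2 × [1 − Φ(1.96 × 5.41 / true SE)].

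| SD (points) | True SE, sub-district | Type I error | True SE, district | Type I error |
|---|---|---|---|---|
| 0 | 5.41 | 5.0% | 5.41 | 5.0% |
| 3 | 5.94 | 7.4% | 6.88 | 12.3% |
| 5 | 6.78 | 11.8% | 8.91 | 23.4% |
| 8 | 8.48 | 21.1% | 12.54 | 39.8% |

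As a second check, the union-only logistic model, without covariates, was fitted to simulated data with the real union layout, 255 women per arm and a union ICC of 0.08 (600 null runs per scenario). The type I error was 4.7% at a sub-district ICC of 0, and 13%, 17% and 27% at 0.01, 0.02 and 0.05.

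**4. Power of a 3 v 3 comparison.** The standard error under the alternative is √(1.5 × 0.4643 / 254.5) = 5.23 points (variance 27.4). This reads 1.5 as the union-level part; sub-district variance is added as 2·SD²/3. Power is from the noncentral t on 4 degrees of freedom (critical value 2.776).

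| Sub-district SD (points) | SE | Noncentrality (14.7 / SE) | Power |
|---|---|---|---|
| 0 | 5.23 | 2.81 | 57% |
| 3 | 5.78 | 2.55 | 49% |
| 5 | 6.64 | 2.22 | 40% |

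**5. Does the 3 v 3 test solve the problem?** Only at sub-district level. Simulating it with no sub-district variance but district SDs of 3, 5 and 8 points gives type I errors of about 9%, 17% and 30%. Between districts the design is 1 v 1, with no degrees of freedom left.

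**The case against.** The strongest reply is that the harm depends on a variance the article does not report. A reader might infer that the type I error necessarily exceeds 5%. The documents do not support that: with no variation above the union the planned test holds its level, and at sub-district SDs of 1 and 2 points the type I error is only 5.3% and 6.1%. The article also argues that Bhola is likely to resemble Chandpur in location, exposure to disasters and care-seeking. It bases significance on an adjusted odds ratio, and the baseline questionnaire records preferred place of delivery, distance to a facility and location of a previous delivery. Adjustment could absorb part of the area variation, and every figure above is unadjusted. All of this stands, and the conclusion has to be conditional.

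It does not remove the point. Expected similarity is not evidence of zero variance, and covariates do not turn unions into separately assigned units. The Introduction itself reports service uptake in the South about 11% below the national estimate, so uptake is known to differ by geography, though this gives no sub-district variance.

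Three further inferences are tempting and go too far.
- **That 1.5 is certainly a union-level figure.** The article gives no level. Its naming of unions as clusters only suggests it, and the implied ICC assumes women spread evenly over all unions.
- **That the stated 80% is miscalculated.** It reproduces. The fall to 57% with no sub-district variance is the price of 4 degrees of freedom.
- **That a 3 v 3 t-test is a fully valid replacement.** It is not if the districts differ (step 5).

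Nor is this detail left to a fuller document: the article itself fixes both the cluster unit and the random effect.

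**Conclusion.** The point holds in conditional form. Assignment is by whole sub-district, with one district per arm, and the stated primary inference recognises only the union. Unless facility delivery does not vary between sub-districts or between the two districts beyond the adjusted covariates, the primary p-value and 95% confidence interval are too favourable. The excess is modest at an SD of 3 points between sub-districts and serious at 8 points, or when the districts themselves differ. These sizes rest on assumed SDs, no adjustment and a design effect of 1.5 taken at union level.

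On that reading of 1.5, the stated 80% power belongs to a union-level analysis with no sub-district variation. An analysis that respects the level of assignment has about 57% at best. No analysis of these six sub-districts can separate the package from a Chandpur-Bhola difference.

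**What to change.** - **Data management and analysis plan:** account for the sub-district in the primary inference, for example by comparing adjusted sub-district proportions 3 v 3 with a t reference on 4 degrees of freedom. Keep the union-only model as a secondary analysis, labelled as conditional on no sub-district or district variation.
- **Sample size:** state the level and ICC behind the design effect of 1.5, and restate the power for the revised primary analysis over a range of sub-district SDs.
- **Study design and Discussion:** state that neither analysis separates the arm effect from a difference between Chandpur and Bhola, so the sub-district analysis is only a partial remedy.

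The cost is a change of wording, wider intervals and a lower stated power, with no extra participants. Restoring 80% power would need more sub-districts; that is a change of design and is not part of this fix.

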### Quality control and quality assurance

We do not anticipate any major deviation from the protocol such as any harm to the participant, or enrollment of participants not eligible for the study. Minor deviations like lost to follow-up will be addressed by enrolling an adequate sample size taking into consideration at an attrition level of 5%. We will communicate with the Ethical Review Board, and trial registries if any major and/or minor deviation occurs during the trial. The data monitoring committee will regularly check data and monitor it to maintain the data quality. An expert will double-check the validation of data collected by the data collectors. The data entry team will link records that have been collected with the help of individual identifiers assigned. We will remove this identifying information once the records are done matching. The anonymized data will be uploaded to a central web-based platform regularly, after following all the appropriate confidentiality requirements. We will use an encrypted, password-protected centralized database system to store data, and only authorized members of the research team will be allowed access.

### Ethics approval

Ethical approval has been taken from the Ethical Review Board of North South University (Ref: 2022/0R-NSU/IRB/0205) (S1 File). After explaining the objectives of the study, the rights of the respondent, and ensuring privacy and confidentiality, we will take written informed consent from the study respondents before data collection. The respondents will have the full right to leave the study at any time during the study period. The data collectors will maintain all necessary precautions (use mask, hand sanitizers and maintain social distancing) during data collection.

### Patient and public involvement statement

We will not involve patients and the public during the study design development phase.

## Discussion

This two-arm non-randomized controlled cluster trial of six months will determine the effect of e-registration tracking and mHealth counseling as a complete package on institutional deliveries in the hazard-prone areas of Southern Bangladesh. A minimum of 268 pregnant mothers of 28–36 weeks will be enrolled and followed up until their deliveries in each intervention and control area. Baseline and end-line data will be used to synthesize the study result. Since the end-line data will be collected four months later than baseline data collection, the study might have a recall bias.

However, to our best knowledge, this two-arm non-randomized controlled cluster trial will be the first study that will evaluate the effect of e-Registration and mHealth as a complete package on institutional deliveries in the hazard-prone areas of Southern Bangladesh. e-registration and mHealth intervention package may increase facility delivery, thus, reduce delivery-related complications and maternal mortality. Thus, our study will facilitate the evidence gap related to the effectiveness of e-registration and mHealth on facility delivery and provide substantial evidence which may help the government to take the necessary steps to roll out e-registration and mHealth counseling as a complete package to increase institutional deliveries and reduce the burden of maternal mortality ratio of Bangladesh by 2030.

## List of abbreviations

ANC: Antenatal care
COVID: 19: Coronavirus Disease-2019
DGFP: Directorate General of Family Planning
FWA: Family Welfare Assistant
MDG: Millennium Development Goal
MMR: Maternal Mortality Ratio
SDG: Sustainable Development Goal
